## 1. Study objectives

Surgery-induced weight loss is linked to reduction of cancer risk but less is known about the effect of weight loss on cancer subtypes and which patient subgroups benefit the most. Previously, the Swedish Obese Subjects (SOS) study reported an association between surgery-induced weight loss and lower cancer incidence in women, but not men. The aim of this study was to further examine the link between surgery-induced weight loss and long-term cancer outcomes, focusing on patient subgroups defined by previously identified predictors to optimize treatment benefit. Metabolic changes, particularly glycaemic biomarkers and extent of weight loss, have been suggested as key factors linking bariatric surgery to reduced cancer risk.

The analyses presented here were conceived post hoc and were not specified in the original study protocol. While the Swedish Obese Subjects (SOS) study was designed as a prospective, controlled intervention trial, with overall mortality as primary outcome, the present analyses were developed after trial completion to address additional hypotheses regarding surgery-induced weight loss and cancer risk. Therefore, the analyses will be regarded as explorative.

## 2. Study Design

### 2.1 Overview

In the SOS study, 4047 individuals with obesity were enrolled at 25 surgical departments and at 480 primary health care centers between 1 September 1987 and 31 January 2001. A bariatric surgery group of 2007 individuals who underwent surgery was formed, along with a prospectively matched control group of 2040 participants. The study is registered at ClinicalTrials.gov (NCT01479452).

### 2.2 Eligibility criteria

The inclusion criteria were ages 37 to 60 years and a body-mass index (BMI) of at least 34 in men and 38 in women before or at the time of the matching examination. The exclusion criteria, designed to exclude patients with unacceptable surgical risks, included previous surgeries for gastric or duodenal ulcers, prior bariatric surgery, gastric ulcer in the past 6 months, ongoing or active malignancy within the past 5 years, myocardial infarction in the past 6 months, bulimic eating patterns, drug or alcohol abuse, psychiatric or cooperative problems contraindicating bariatric surgery, other contraindicating conditions (such as chronic glucocorticoid or anti-inflammatory treatment).

### 2.3 Data collection and follow-up

Baseline examinations took place 4 weeks before the intervention started. Follow-up visits, which included physical examinations and questionnaires, were scheduled at 0.5, 1, 2, 3, 4, 6, 8, 10, 15, and 20 years. Fasting blood samples were collected at baseline and after 2, 10, 15 and 20 years.

Register-based health outcomes will be collected through register-linkage from the Swedish national registries, using unique personal identification numbers in Sweden.

### 3. Study outcomes

Cancer, death, and emigration data will be obtained by linking SOS participants to national registers. Information on deaths and emigration will be obtained from the Swedish Cause of Death Register and the Swedish Population and Address Register (SPAR).

Information on cancer events will be obtained from The Swedish Cancer Registry, which covers over 95% of malignant tumors, with 99% morphologically verified.

Obesity-related cancers will be defined according to the IARC, and include esophageal adenocarcinoma, postmenopausal breast cancer, cancers of the kidney, colon/rectum, gastric cardia, liver, gallbladder, pancreas, ovary and thyroid, endometrial cancer, multiple myeloma, and meningioma. Other cancers will be classified as non-obesity related. Female-specific cancers include breast, ovarian, endometrial, cervix, and all other gynecological cancers.

All registers are up to date including 31.12.2022.

### 4. Statistical methods

Baseline characteristics will be compared using t-tests (continuous variables) and Fisher's exact test (dichotomous variables). BMI changes will be analyzed with multilevel linear mixed-effects regression models, separately for men and women. The observations will be considered nested within the individuals, and the confidence intervals (CIs) will be calculated taking the repeated measurements into account.

Patients will be analyzed according to their received intervention (i.e. participants will be included in their original study group until any bariatric surgery happens in the control group or there will be a change in, or removal of, the bariatric surgical procedure in the surgery group).

Participants will be followed until the first occurrence of cancer, death, emigration, or end of register-based follow-up (December 31st, 2022). Those who emigrated, died or remained event-free at the end of follow-up will be treated as censored observations in the analyses. In addition, control-group participants who underwent bariatric surgery during follow-up and surgery-group patients who had a procedure restoring normal anatomy will be censored from the analyses at the time point of these operations.

Kaplan-Meier estimates will be used to compare time to first cancer diagnosis or cancer-related death across treatment groups. Cox proportional hazards models will be used to calculate hazard ratios for surgical treatment effects on overall, obesity-related, and female-specific cancers. The proportional-hazards assumption will be evaluated by assessing the interaction between treatment and the logarithm of time. When the assumption is not fulfilled, Cox regression models will be modified to include time-varying effects. Restricted Mean Survival Time (RMST) approach will be used to compare cancer-free time between the surgery and control groups.

To account for baseline differences between the surgery and control groups, analyses will be adjusted for major cancer risk factors defined by the American Cancer Society, age, sagittal diameter, alcohol consumption, and smoking. In addition, serum insulin levels, which have previously been associated with cancer risk in sub-analyses in the SOS study, will be adjusted for. All covariates are selected a priori the actual analyses and will be included in the models regardless of their actual statistical significance.

To formally test whether baseline insulin modifies the effect of bariatric surgery on cancer risk, an interaction term using the continuous insulin variable will be included in the Cox proportional hazards models. For descriptive purposes, cancer incidence and mortality across subgroups defined by the tertiles of baseline insulin were presented.

The association between weight change and cancer risk will be assessed using the Cox proportional hazard regression model, including one year weight change in the models. These analyses will be restricted to the surgery group only.

In sensitivity analyses, participants with a history of cancer before study inclusion and participants with a cancer event within the first three years after inclusion to the study will be excluded.

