## 5. Version history

**Version 4, 2025-10-01 (current version):** Additional analyses included during a review process: more detailed analyses on time-varying risk; added analyses with restricted survival-time approach.

**Version 3, 2024-11-15:** Included analyses on cancer types (obesity-related cancers; female-specific cancers). Analyses on association between weight change and cancer risk in the surgery group added. Register-data was updated to include data until 31.12.2022. Analysis of case-fatality removed.

**Version 2, 2023-04-03:** Added analyses on cancer mortality, based on reviews of case sheets and autopsy reports. Sensitivity analyses added. Analyses on case-fatality included. More details on statistical methods added.

**Version 1, 2021-01-14:** First version focusing on time to total cancer incidence (fatal and non-fatal) in the surgery and control groups.

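### The SAP's one follow-up and censoring rule fits time to first cancer but contradicts its planned use of cancer-related death; applied literally, no cancer death is ever an event.

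*SAP*

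**What the plan says.** SAP section 4 (Statistical methods) states when observation ends: "Participants will be followed until the first occurrence of cancer, death, emigration, or end of register-based follow-up (December 31st, 2022"). The next sentence says who is censored: "Those who emigrated, died or remained event-free at the end of follow-up will be treated as censored observations in the analyses". A further sentence adds censoring at bariatric surgery in controls and at restoring operations in the surgery group. None of these sentences is limited to a particular endpoint.

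The same section then uses cancer death twice:

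- For the group comparison: "Kaplan-Meier estimates will be used to compare time to first cancer diagnosis or cancer-related death across treatment groups".
- For the insulin subgroups, as description: "cancer incidence and mortality across subgroups defined by the tertiles of baseline insulin were presented".

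The SAP gives no separate follow-up or event rule for cancer mortality. Its section 5 (Version history) records for version 2: "Added analyses on cancer mortality, based on reviews of case sheets and autopsy reports". For version 3 it records "Analysis of case-fatality removed", and no entry says that cancer mortality was withdrawn.

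**The concern.** An event and a time at risk have to be defined for each endpoint. Stopping at the first cancer is the usual choice for incidence, because the event has then occurred. For cancer mortality the same stop removes a participant at the moment when the risk of cancer death begins to matter. Censoring all deaths then removes the rest of the endpoint.

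An analyst who follows the text has no mortality events to analyse. An analyst who departs from it must decide, without a written rule, whether follow-up continues after diagnosis and how deaths from other causes are handled. Those choices can give different mortality curves in two groups that were matched, not randomised. A reader of the results could not tell from the SAP which choice was made.

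**Working it through.** The SAP states no event count, power or sample size for this endpoint, so there is no figure to reproduce. The check applies the section 4 rule to each possible course. The crossover operations and emigration are left aside, since they end follow-up without an event under any reading.

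| Course | Follow-up ends at | Status under the written rule | Status needed for cancer mortality |
|---|---|---|---|
| A. Cancer diagnosed, later dies of it | diagnosis | cancer event; the death falls outside follow-up | event at death |
| B. Dies of cancer, no earlier recorded diagnosis | death | censored, as having died | event at death |
| C. Cancer diagnosed, later dies of another cause | diagnosis | cancer event | no event, follow-up to death |
| D. Dies of another cause, never had cancer | death | censored | no event, follow-up to death |
| E. Alive and cancer-free at the end | 31 December 2022 | censored | no event |

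Every cancer death belongs to A or B. Let *a* and *b* be the numbers in those rows.

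1. **Rule as written.** Cancer deaths counted as events = 0 × *a* + 0 × *b* = 0. This holds for any *a* and *b*, so it rests on no assumed rate.
2. **Only the death-censoring sentence relaxed**, with follow-up still ending at diagnosis. Events = *b*, out of *a* + *b*. The share *b*/(*a* + *b*) cannot be calculated from the SAP.
3. **Both sentences made endpoint-specific.** Events = *a* + *b*, which is what a cancer-mortality analysis needs.

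The Kaplan-Meier sentence can also be read as one composite endpoint: first diagnosis, or cancer death where there was no diagnosis. Row A is then handled correctly, because its event is the diagnosis. Row B is still wrong: the composite needs an event and the rule gives a censored time. The composite reading also leaves the tertile sentence unexplained, since that sentence names mortality beside incidence.

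For the other analyses, first-cancer incidence needs an event at diagnosis in A and C and no event in D and E, and the rule delivers this. Row B could matter there only if incidence is meant to include cancers first known at death.

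**The case against.** The strongest reply is that the rule was written for incidence and any competent analyst would see that. The version history supports this: version 1 dealt with total cancer incidence, and mortality came in with version 2. The composite reading is also natural for the Kaplan-Meier sentence, which leaves separate mortality certain only in the descriptive tertile sentence. Section 1 of the SAP describes the whole set of analyses as post hoc and exploratory. Much of this stands, and it lowers the weight of the point. It does not remove the contradiction: the rule is stated for the analyses in general, the composite still loses row B, and the tertile sentence still has no rule. The protocol is unlikely to supply one, because section 1 says that these analyses were not in the original protocol.

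A reader might infer more than the SAP supports:

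- **That mortality results cannot be obtained.** Section 3 takes deaths from national registers and says that all registers run to 31 December 2022. The information exists; only the written rule fails to use it.
- **That only about 5% of cancer deaths could count.** Section 3 describes the Cancer Registry as one "which covers over 95% of malignant tumors, with 99% morphologically verified". That is coverage of tumours. It is not the share of cancer deaths with an earlier registered diagnosis, and fatal cancers may be covered better or worse. Applying 1 − 0.95 = 0.05 to deaths puts the answer in as an assumption. The SAP also gives no total of cancer deaths from which to form a count.
- **That mortality would be compared without covariate adjustment.** The Cox sentence does not name mortality, but the adjustment sentence in section 4 covers the analyses without limit. The text is unclear, so this cannot be stated as fact.
- **That omission from section 3 is an error.** That section gives data sources and cancer-type definitions and is not a formal list of endpoints.
- **That a competing-risks or Cox analysis of mortality is required.** Censoring deaths from other causes gives a legitimate cause-specific hazard, and a descriptive report is acceptable in an exploratory plan. What is needed is a statement of the choice.

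**Conclusion.** The contradiction is real and stands on the current text of section 4. Applied literally, the rule gives 0 cancer-death events, and that result depends on no assumption about rates. If only the death-censoring sentence is relaxed, the mortality analysis keeps just the cancer deaths without an earlier recorded diagnosis. The SAP does not allow that number to be estimated, so none is given here.

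The reach is limited to the cancer-death part of the Kaplan-Meier analysis and the cancer mortality by insulin tertile. The Cox models for cancer incidence, the RMST comparison of cancer-free time, the insulin interaction and the weight-change analysis are largely unaffected. The reservation concerns only the handling of cancers first known at death. For exploratory analyses this is a correction to make before any mortality result is relied on. It does not put the incidence results in doubt.

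**What to change.** Replace the single rule in SAP section 4 with one for each endpoint:

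- **Incidence:** follow to the first cancer after inclusion. If the Kaplan-Meier endpoint is the composite of first diagnosis or cancer death, say so and count a cancer death without an earlier diagnosis as an event at the date of death.
- **Cancer mortality:** follow from inclusion to death from cancer, without stopping at diagnosis. End follow-up without an event at death from another cause, emigration, the crossover operations already named, or 31 December 2022. State whether death from another cause is censored or treated as a competing event.
- **Censoring of deaths:** limit it to deaths that are not the endpoint of the analysis in question.

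The tertile sentence is in the past tense, so mortality results may already exist. If they do, the SAP should record the rule that was used, mark it as a later clarification, and have the results re-run if that rule differs from the corrected one.

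The cost is a few sentences and the re-derivation of one time-to-event variable from registers that the plan already links. No new data are needed.

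### Censoring non-cancer deaths over 22 to 35 years of potential follow-up leaves the RMST for cancer-free time measuring neither time alive without cancer nor time lost to cancer, and 1−KM too high if read as risk

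*SAP*

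**What the plan says.** SAP section 4 (Statistical methods) sets one censoring rule for the time-to-event analyses: "Those who emigrated, died or remained event-free at the end of follow-up will be treated as censored observations in the analyses". The same section then plans two summaries built on survival curves:

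- "Kaplan-Meier estimates will be used to compare time to first cancer diagnosis or cancer-related death across treatment groups"
- "Restricted Mean Survival Time (RMST) approach will be used to compare cancer-free time between the surgery and control groups"

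The SAP names no cumulative incidence function, competing-risk method or composite of cancer and death, and gives no truncation time for the RMST.

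Three other statements bear on the point. Section 2.1 dates enrolment "between 1 September 1987 and 31 January 2001", and section 3 says "All registers are up to date including 31.12.2022". Section 2.2 gives the entry age: "The inclusion criteria were ages 37 to 60 years". Section 1 describes the parent study as a trial "with overall mortality as primary outcome".

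**The concern.** A person who dies without cancer accrues no more cancer-free time and can no longer develop cancer. Censoring treats that person as still at risk, with the same future cancer hazard as those who remain under observation. The resulting curve describes a population without other-cause death, and does so only if such death is independent of cancer risk. The area under it is neither the mean time alive and free of cancer nor the horizon minus the mean time lost to cancer.

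Three features make this more than a technicality here. Potential follow-up is long and participants reach old age. Overall mortality was the outcome that the parent study set out to change, so equal distortion in both groups cannot be presumed. And RMST is the only summary in the plan on a time scale, so readers are likely to take its result literally.

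**Working it through.** The SAP states no event rate, risk or RMST value on this point, so there is no figure of its own to reproduce.

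**Step 1. Potential follow-up (dates in sections 2.1 and 3).** 1 September 1987 to 31 December 2022 is 12,905 days / 365.25 = 35.3 years. 31 January 2001 to 31 December 2022 is 8,004 / 365.25 = 21.9 years. Survivors are then about 37 + 21.9 = 59 to 60 + 35.3 = 95 years old. Everyone could reach 20 years. Nobody enrolled after 31 December 1992 could reach 30. These are potential, not observed, times.

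**Step 2. Direction.** Let c(t) be the cancer hazard and d(t) the hazard of non-cancer death, with cumulative hazards C(t) and D(t), and horizon τ.

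- 1−KM with deaths censored: 1 − exp(−C(τ))
- Cumulative incidence (CIF): ∫₀^τ c(t) exp(−C(t) − D(t)) dt
- RMST with deaths censored: ∫₀^τ exp(−C(t)) dt
- Mean time alive and cancer-free: ∫₀^τ exp(−C(t) − D(t)) dt
- Restricted mean time lost to cancer: ∫₀^τ CIF(t) dt

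Whenever D(t) > 0, 1−KM exceeds the CIF. That direction needs no assumed rate.

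**Step 3. Hand check with constant hazards (assumed c = d = 1.0% a year, τ = 30).** 1−KM = 1 − exp(−0.30) = 25.9%. CIF = (0.01/0.02)(1 − exp(−0.60)) = 22.6%. RMST with deaths censored = 0.259/0.01 = 25.9 years. Time alive and cancer-free = (1 − exp(−0.60))/0.02 = 22.6 years. τ minus the area under the CIF = 30 − 0.5 × (30 − 22.56) = 26.3 years. The three time measures all differ.

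**Step 4. Group contrasts with hazards rising with time.** All inputs are assumptions: cancer hazard 0.4 or 0.6% a year at entry, growing 3.5% a year; non-cancer death 0.4% a year at entry, growing 7% a year; cancer HR 0.8; death HR 0.7 or 0.85. The formulas were integrated numerically, and ratios come from unrounded values.

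| τ (years) | Cancer hazard at entry | Death HR | Risk difference, 1−KM (points) | Risk difference, CIF (points) | Ratio | RMST difference, deaths censored (years) | Difference in time lost to cancer (years) |
|---|---|---|---|---|---|---|---|
| 20 | 0.4% | 0.70 | 2.08 | 1.75 | 1.184 | 0.191 | 0.173 |
| 20 | 0.4% | 0.85 | 2.08 | 1.84 | 1.126 | 0.191 | 0.178 |
| 20 | 0.6% | 0.70 | 2.96 | 2.49 | 1.185 | 0.278 | 0.252 |
| 20 | 0.6% | 0.85 | 2.96 | 2.63 | 1.125 | 0.278 | 0.259 |
| 30 | 0.4% | 0.70 | 3.48 | 2.40 | 1.452 | 0.467 | 0.385 |
| 30 | 0.4% | 0.85 | 3.48 | 2.71 | 1.286 | 0.467 | 0.408 |
| 30 | 0.6% | 0.70 | 4.75 | 3.27 | 1.454 | 0.662 | 0.546 |
| 30 | 0.6% | 0.85 | 4.75 | 3.70 | 1.282 | 0.662 | 0.580 |

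**Step 5. Two variants at 30 years.** With equal mortality (death HR 1.0), the risk difference is still overstated, by about 15%. With cancer HR 1.0 and death HR 0.7 to 0.85, the Kaplan-Meier curves coincide, while the CIF is 0.4 to 1.0 points higher with surgery because more people survive to develop cancer.

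**The case against.** Several stronger readings are tempting, and the SAP does not support them.

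- **That the treatment effects are invalid.** Censoring deaths is the standard route to a cause-specific hazard ratio. The Cox models carry the main effects, the insulin interaction and the weight-change analysis, and none of these is undermined.
- **That the plan will report inflated absolute risks.** Section 4 uses Kaplan-Meier to compare groups and never says that 1−KM will be presented as risk. The overstatement arises only if the curves are read that way.
- **That every death is mishandled.** Death from cancer is an event in the Kaplan-Meier endpoint, so only non-cancer deaths are at issue. The blanket censoring of those who died needs reconciling with that endpoint.
- **That the benefit is overstated by a third to a half.** Figures of that order belong to 30 years under assumed rates, a horizon that many participants cannot reach. At 20 years the RMST difference with deaths censored and the difference in time lost to cancer are 0.01 to 0.03 years apart.
- **That the correct RMST must count death as an event.** Under the same assumptions that composite differs by 0.83 to 1.40 years at 30 years, but this is a different question, not a bias correction. With cancer HR 1.0 it would still show 0.40 to 0.88 years in favour of surgery, all from mortality. A cancer-specific contrast suits the aim in section 1.

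It is also fair that the analyses are declared post hoc and exploratory, and that RMST entered only in Version 4. Neither point resolves the mismatch between the quantity named and the quantity the censoring rule delivers.

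**Conclusion.** The concern holds in a limited form and should be fixed. Applied as written, the censoring rule makes the RMST a hypothetical quantity that does not match its label, and makes 1−KM exceed cumulative incidence.

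Only that direction is certain. The size rests on assumed cancer and death rates and on assumed group differences in both, since the SAP supplies none. On those assumptions the effect is modest at 20 years (risk difference too large by about 13 to 18%, or 0.2 to 0.5 points) and material at 30 years (28 to 45%, or 0.8 to 1.5 points). Whether the groups are distorted unequally depends on mortality that the SAP does not report.

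**What to change.** In SAP section 4:

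1. For any absolute risk, replace 1−KM with Aalen-Johansen cumulative incidence, treating non-cancer death as the competing event.
2. Report the RMST contrast as restricted mean time lost to cancer, from the cumulative incidence curve, at a stated truncation time that every participant could reach, for example 20 years.
3. Optionally add RMST on survival free of both cancer and death, labelled as a composite that also reflects mortality.
4. Label the Cox hazard ratios cause-specific.
5. Reword the censoring rule so that it agrees with cancer-related death being an event.

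The cost is a few sentences and a little more analysis with standard software. Section 3 already plans linkage to the registers for cancer and death. The downside is that the absolute cancer benefit may look slightly smaller.

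### Sex is not named in the Cox adjustment set and no cancer analysis is split or tested by sex; the cost is missing sex-specific estimates and an undefined risk set more than bias in the pooled hazard ratio

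*SAP*

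**What the plan says.** All references are to the SAP.

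- **Adjustment set (Section 4).** "analyses will be adjusted for major cancer risk factors defined by the American Cancer Society, age, sagittal diameter, alcohol consumption, and smoking". Insulin follows: "In addition, serum insulin levels, which have previously been associated with cancer risk in sub-analyses in the SOS study, will be adjusted for". The set is closed: "All covariates are selected a priori the actual analyses and will be included in the models regardless of their actual statistical significance".
- **Effect modification (Section 4).** For baseline insulin, "an interaction term using the continuous insulin variable will be included in the Cox proportional hazards models", with a descriptive display by insulin tertile. The other interaction mentioned, treatment by log time, is a proportional-hazards check.
- **Sex-separated analysis (Section 4).** "BMI changes will be analyzed with multilevel linear mixed-effects regression models, separately for men and women". This is not a cancer outcome.
- **Endpoints (Sections 3 and 4).** Cox models are planned for overall, obesity-related and female-specific cancers. The obesity-related group includes postmenopausal breast, ovarian and endometrial cancer. Nothing restricts the female-specific analyses to women.
- **Background and aim (Section 1).** The earlier SOS work "reported an association between surgery-induced weight loss and lower cancer incidence in women, but not men". The present aim is to look further, "focusing on patient subgroups defined by previously identified predictors to optimize treatment benefit".
- **Entry criteria (Section 2.2).** Both sexes were enrolled, under different limits: "a body-mass index (BMI) of at least 34 in men and 38 in women".

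**The concern.** Sex is the one factor for which the SAP itself reports a differing association between surgery-induced weight loss and cancer. Even so, no cancer analysis adjusts for it by name, stratifies on it, or estimates the surgery effect within it. Two of the three cancer endpoints mix sites that occur in both sexes with sites that occur essentially only in women, so baseline hazards plausibly differ by sex.

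Three things are at stake:

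1. The reader gets one pooled hazard ratio and cannot see whether it describes women, men or both.
2. The model of one-year weight change and cancer uses surgery patients only. If weight change differs by sex, sex can confound that association.
3. If men are kept in the analysis of female-specific cancers, they add follow-up time with almost no events. That lowers absolute risks and shrinks absolute contrasts.

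**Working it through.** The SAP gives no event counts, sex split, power or alpha for this point, so there is no plan figure to reproduce. The check is a count from the text, followed by three sizing steps on stated assumptions.

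**1. Count from the text.**

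| Item | Planned | Involving sex |
|---|---|---|
| Named Cox covariates | 5 (age, sagittal diameter, alcohol, smoking, insulin) | 0 |
| Treatment interactions with a baseline factor | 1 (insulin) | 0 |
| Sex-separated analyses | 1 (BMI change) | 0 for a cancer outcome |

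**2. Pooled treatment hazard ratio.** A simulation used the SAP's group sizes (2007 and 2040) and 60 replicates. It assumed 70% women, a treatment hazard ratio of 0.75 in women and 1.0 in men, and a female-to-male cancer hazard ratio of 1.2, 1.5 or 2.0. None of these assumptions is in the SAP.

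| Female:male hazard ratio | Treatment HR, sex omitted | Treatment HR, stratified by sex | Ratio |
|---|---|---|---|
| 1.2 | 0.818 | 0.817 | 1.001 |
| 1.5 | 0.814 | 0.806 | 1.010 |
| 2.0 | 0.801 | 0.785 | 1.020 |

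Omitting sex moves the treatment hazard ratio by 0.1%, 1.0% and 2.0%.

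The stratified values can be approximated by hand. The pooled log hazard ratio is roughly an event-weighted average, so HR ≈ 0.75^w, where w is the share of events in women: w = 0.7r / (0.7r + 0.3), with r the female:male hazard ratio.

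- r = 1.2: w = 0.84/1.14 = 0.737, HR ≈ 0.81
- r = 1.5: w = 1.05/1.35 = 0.778, HR ≈ 0.80
- r = 2.0: w = 1.40/1.70 = 0.824, HR ≈ 0.79

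These lie close to the simulated values. The pooled figure falls between 0.75 and 1.0 because that heterogeneity was assumed, and stratifying the baseline hazard does not remove the averaging. Only sex-specific estimates do.

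**3. Power of a treatment-by-sex test.** The same simulation gave 0.38, 0.30 and 0.33. With 60 replicates, the Monte Carlo standard error near 0.33 is √(0.33 × 0.67 / 60) = 0.06. The three values cannot be told apart; the usable reading is roughly one third under these assumptions.

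**4. Female-specific cancers with men retained.** Let p be the proportion of women, equal in both arms, and treat men as having no risk. Men then contribute the full time horizon in each arm, so their RMST difference is zero:

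pooled RMST difference = p × (difference in women) + (1 − p) × 0 = p × (difference in women).

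At an assumed p of 0.6 to 0.8, the pooled difference is 0.6 to 0.8 times the difference in women. Differences in Kaplan-Meier cumulative incidence shrink by about the same factor. The Cox hazard ratio is less exposed: with equal p in both arms the factor cancels approximately, but with unequal p it becomes roughly the ratio of the two proportions times the true hazard ratio.

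**5. Weight-change model.** Confounding needs sex to be related both to one-year weight change and to cancer hazard. The SAP allows for the first by modelling BMI change separately by sex. The endpoint definitions make the second plausible. Matching between arms cannot help, because only one arm is analysed. The SAP gives nothing from which to derive the size or direction of the bias.

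**The case against.** There are several fair points in favour of the plan.

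- **The American Cancer Society phrase may cover sex.** It can be a heading for the listed items or a separate, unlisted set. On the second reading sex might be included. This stands as a limit on certainty: the SAP does not name sex, but it cannot be shown to exclude it. A set declared fixed in advance should be listed in full.
- **Controls were prospectively matched (Section 2.1).** The variables are not given in the SAP. If sex was one, confounding of the between-arm hazard ratio would be limited. That stands, but matching neither estimates effect modification nor helps the surgery-only model or the female-specific risk set.
- **Testing the sex difference is not a stated aim.** The earlier result in women is background. Section 1 names glycaemic biomarkers and extent of weight loss as key factors, and both are analysed. This stands, so the plan does not fail a declared objective. But sex is a previously reported predictor, and a subgroup-oriented plan that opens with it leaves a gap by giving no estimate.
- **The analyses are post hoc and exploratory, and an interaction test would be weak.** Both stand, and they argue for presenting the result as estimation.

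A reader might infer that the pooled hazard ratio is materially biased, or wrong for both sexes. The documents do not support that. The illustrative shift is at most about 2%, and lying between two sex-specific values is a property of any average effect once different effects have been assumed. A reader might also infer harm from sex acting through sagittal diameter. That variable is only an adjustment covariate, and the SAP nowhere makes its coefficient a quantity of interest.

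**Conclusion.** The point holds in limited form. Sex is not named in the fixed adjustment set, and no cancer analysis is split or tested by sex. The expected effect on the pooled treatment hazard ratio is small: about 0 to 2% under the assumed inputs, and less if matching covered sex. The simulation is only illustrative, since the SAP supplies neither the sex split nor the sex-specific risks.

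What matters is threefold: no sex-specific estimate of the surgery effect on cancer, possible confounding by sex in the weight-change model (size unknown), and dilution of the absolute contrasts for female-specific cancers if men are retained (a factor of 0.6 to 0.8 at an assumed 60 to 80% women). The last depends on reading the SAP literally. The analysts may intend a women-only analysis, but the text does not say so.

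The change should be made. It does not invalidate the main analysis.

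**What to change.** 1. List every covariate explicitly and say whether the American Cancer Society phrase adds any.
2. Stratify the baseline hazard by sex in every Cox model that includes both sexes, including the weight-change model.
3. For overall and obesity-related cancer, report sex-specific treatment hazard ratios with confidence intervals and a treatment-by-sex interaction, labelled exploratory.
4. Restrict all female-specific cancer analyses (Kaplan-Meier, Cox and RMST) to women.

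The cost is SAP wording and reruns on data already held. The downside is an interaction test with limited power, so it should be presented as estimation with intervals. A non-significant result should not be read as evidence of equal effects in men and women.
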